## Abstract

**Background:**

The quality control of oral anticoagulant therapy (OAT) during the initiation and maintenance treatment is generally poor. Physicians' ordering of OAT (especially *fluindione *and *warfarin*) can be improved by dose adjustment algorithms, taking into account the results of International Normalized Ratio (INR). Reminders at the point of care, computerized or not, have been demonstrated to be effective in changing physicians prescription behavior.

However, few studies have addressed the benefit of personalized reminders versus non personalized reminders, whereas the personalized reminders require more development to access patient record data and integrate with the computerized physician order entry system.

The Hospital Information System of George Pompidou European Hospital integrates an electronic medical record, lab test and drugs order entry system. This system allows to evaluate such reminders and to consider their implementation for routine use as well as the continuous evaluation of their impact on medical practice quality indicators.

The objective of this study is to evaluate the impact of two types of reminders on overtreatment by oral anticoagulant: a simple reminder of text formatted dose adjustment table and a personalized recommendation for oral anticoagulant dose and next date of INR control, adapted to patient data. Both types of reminders appear to the physician at the moment of drug ordering.

**Methods:**

The study is an alternating time series experiment with three 6 months periods, each one including every 2 months according to a Latin square scheme: a control period without any reminder, a period with the simple non personalized reminder, a period with personalized reminder. All patients hospitalized in departments using the computerized physician order entry system and ordered *fluindione *or *warfarin*, will be included in the study between November 2004 and May 2006.

Main outcome will be the proportion of overcoagulation, as expressed by the proportion of observation time with INR over 4.5, assuming INR change linearly. Secondary outcome is the incidence of major haemorrhagic events. Data will be collected thanks to Hospital Information Systems databases.

Data will be analyzed taking into account patient and physician clustering effect.

## Background

### Iatrogenic effects of oral anticoagulants therapy

According to a study carried out by French pharmacovigilance centres, haemorrhage subsequent to oral anticoagulant treatment (OAT) is the most common drug-related side effect resulting in hospitalisation in public hospitals in France (13% of such admissions, and 0.41% of the 3,137 admissions analysed). On the basis of these findings, the AFSSAPS (French Agency for Health Product Safety) has made the prevention of iatrogenic effects related to OAT one of its priorities. Many of these events are consequences of interactions between different drugs, resulting in inappropriate doses [1-3].

Implementation of a system of support when prescriptions are made out is likely to improve prescription practices and to decrease the frequency of side effects. It should be possible to integrate a support tool into the drug prescription system, by using nomograms to adjust OAT doses.

### Decision-making tools and appropriate practice

The efficiency of reminders issued at the time of prescription has been demonstrated by a various studies [4-8]. These reminders can come in a paper, telephone [9] or computer form. Hunt *et al*. [10] reviewed all studies (randomised and quasi-randomised) evaluating the effect of computer-based clinical decision support systems on medical practice and treatment outcome. They showed that these systems are effective for drug prescription purposes and for the implementation of various medical strategies [10]. We have demonstrated the efficiency of reminders in the French situation, both in the form of "paper" reminders [11] and in the form of computer-generated reminders [12]. Computer-generated reminders appear the most promising given the development of computer programs including prescription aids for hospital usage.

Several types of reminders can be issued at the time of prescription [13]:

• simple, general information concerning the recommendations that should be taken into account (non-specific or non-personalised reminders),

• "check list": includes questions or a precise list of practices that the doctor must tick to show that it has been done,

• reminders including clinical data concerning a specific patient that must be taken into account for a given procedure (personalised reminders).

The advantage of personalised reminders over non-personalised reminders has not been demonstrated in the literature. However, the production of personalised reminders necessitates better integration of existing information and is thus more expensive to develop. It is important to determine whether this personalised tool results in a better quality of care than non-personalised tools.

Several randomised clinical trials have tried to evaluate decision support systems for the prescription of OAT, but failed to draw any conclusions about their efficiency for several reasons: heterogeneity and complexity of the systems evaluated, experimental designs difficult to apply and not necessarily adapted, and too few patients included [14-17].

Reminders issued at the time of prescription have been shown to be effective by experimental studies, but the difficulties of maintaining the effectiveness of interventions designed to improve clinical practices remains a major problem. We evaluated the effect of an active decision support system for the prescription of low molecular weight heparin as prophylaxis for venal thrombosis in an orthopaedic surgery department. In this study, the system was and was not used during alternate periods. It showed that such programs affect practices without affecting learning [12]. Other authors have looked at the problem of the routine use of computerised systems [18,19]. The long-term use of a computer program to modify medical practices necessitates a hospital information system that ties in prescriptions and the results of medical tests, and the continuous collection of indicators making it possible to evaluate use and effect.

### Georges Pompidou European Hospital (GPEH)

#### Organisation of the information system at GPEH

The hospital information system currently collates prescriptions and results of biological tests and imaging procedures. Eight hundred computers, both laptops and fixed posts, are used to in care procedures (in care departments and medical offices).

The Dx-Care^® ^program is at the centre of care delivery. It is used by doctors and nurses:

• to prescribe laboratory examinations and imaging tests for a patient,

• to visualise the results of laboratory tests,

• to establish and to consult nursing schedules,

• to archive a structured observation,

• to prescribe drugs.

Dx-Care^® ^is integrated with other applications to allow circulation of information between departments, laboratories and the pharmacy. Prescriptions for laboratory tests are transmitted to the Netlab^® ^program which manages such tests (this program is used by all biochemistry, haemostasis and immunology laboratories, etc.) The laboratories return the results using this same program, which retransmits them to Dx-Care^®^. Furthermore, prescriptions of drugs are transmitted to the Phedra program, which is used by the pharmacy to manage prescriptions. The prescription is validated by the pharmacy and this validation is then transferred to Dx-Care^®^. The lab test prescription facility has been available in the hospital information system since 2000 and is used by all departments of the hospital. The drug prescription facility has been implemented later on, since January 2003, and its use is still increasing (currently by half of the hospital departments).

The hospital information system thus allows to install decision support systems that are activated whenever a prescription is issued and routinely to collect evaluation criteria of prescription practices. If possible and validated, the use of the hospital information system to evaluate care procedures will make it possible to collect data regularly, and routinely to assess methods for the improvement of care practices.

#### Organisation of quality assurance and system for recording undesirable events

With the aim of quality of care and preventing risks, the hospital is developing a system, based on the Intranet network, of declaration of undesirable events. This system must be able to record all undesirable events and incidents linked to the use of health products (drugs, medical equipment, blood products, etc.) and care (e.g. falls, lost files, bedsores, long waiting times) as well as those due to the patient environment (building, security, malevolence, etc.) and the job of health care professionals (accidental exposure to blood, chemicals, radiation, etc.).

When a health care professional decides to report an undesirable event, he or she must complete a dedicated form available on the Intranet with all relevant information. This incident form includes an item entitled "complications associated with anti-coagulants". When the doctor clicks on this item, a form specific to haemorrhagic accidents following anti-coagulant treatment appears (see form in appendix).

#### Prevention of thrombosis at GPEH

Among departments which already started to use the computerised drug order entry system, several (cardiology and vascular medicine departments) are heavy "consumers" of anti-thrombosis drugs (see Table 1).

In 2001, a working group representative of all the hospital departments described a group of procedures. This was done by critically reading articles published in the literature. The procedures concerned the preventive and curative indications of anticoagulants (OAT and heparins) in arterial thrombosis and venous thrombosis, and the way in which patients receiving anticoagulants are monitored and handled in cases of overdose. The procedure concerning curative OAT included a nomogram for adjusting doses of *fluindione *and *warfarin *based on previous doses and the INR (see Tables 2 and 3). These nomograms are currently available on the hospital's intranet, although they are not widely used. Their inclusion in a computerised prescription aid could increase their impact.

### Study aims

#### Main aims

1. To evaluate the effect on the frequency of overanticoagulation of the implementation in the computerised physician order entry system of two types of tool to adjust OAT doses (one personalised and one non-personalised).

2. To assess any advantages of using the personalised tool rather than the non-personalised tool.

#### Secondary aims

1. To evaluate the frequency of haemorrhagic accidents in the context of the study.

2. To evaluate the feasibility of long-term implementation of the intervention.

## Methods

### Experimental design

The study is an alternate time series experiment which consists of three successive six-month periods (timed to change with the changing of medical residents even though they will not be the only prescribers). Each phase will consist of:

• a two-month period without active support during which evaluation criteria will be collected (period A),

• a two-month period with non-personalised active support (period B),

• a two-month period with personalised active support (period C).

To limit the impact of a learning effect on appropriate OAT management practice within the department over time (possible for medical residents), the order of these three periods was determined by using a Latin square plan (see Figure). This experimental design can be considered valid for an impact study in this context whereas a randomised controlled design is difficult to apply with just one hospital [20].

### Participants

#### Patients

This study will include all the patients who are prescribed OAT for any indication and are hospitalised in clinical care departments where physicians are using the hospital information system to prescribe drugs.

The following table shows the number of INR examinations prescribed by these departments in a three-month period. It provides an estimation of the approximate proportion of overdoses among the INR that exceeded 2, which is supposed to be found in patients treated with OAT in these units.

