#### Number of INR measurements and predicted frequency of overdoses

During a six-month period (January to June 2004), 4 920 INRs were requested by the six departments which already routinely use the computerized physician order entry system. The frequency of overtreatment can approximately be estimated from the percentage of INR > 4.5 among INR >2. Among the 2620 INR > 2, 330 (12%) were higher than 4.5 (see Table 4). This frequency has been stable during these six months but differed considerably between departments (10% to 23%).

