### Statistical analyses

Statistical analyses will be performed with the STATA statistical software (release 8, STATA corp, College station, Tex, USA)

Standard statistical tests will be used to compare the baseline characteristics of the departments and patients.

The main analysis concerns the effect of the intervention on the number of dangerously high INRs. The analysis will be carried out using a mixed effect analysis of variance model, in which the effect linked to the period will be considered fixed and that linked to the prescription tool will be considered random [22].

Rosendaal's method will be used to analyse the number of patient-days with INR over the target [21].

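### The main model has no department term although the set of departments is not fixed, so a change in department mix inside a semester can bias the tool contrasts

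*Protocol article*

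**What the plan says.** - **Design.** Under Experimental design: "The study is an alternate time series experiment which consists of three successive six-month periods". Each contains a two-month block with no support (A), one with the non-personalised tool (B) and one with the personalised tool (C), and "the order of these three periods was determined by using a Latin square plan". The stated reason for the square is to limit the impact of learning over time. No concurrent control is described; the figure with the schedule is not shown.
- **Who is included.** Under Participants, Patients: all patients prescribed oral anticoagulants who are "hospitalised in clinical care departments where physicians are using the hospital information system to prescribe drugs". No closed list or cut-off date is given.
- **Spread of order entry.** The Background section on the hospital's information system says of the drug prescription facility that "its use is still increasing (currently by half of the hospital departments").
- **Planning data.** In the sample size section, "4 920 INRs were requested by the six departments which already routinely use the computerized physician order entry system" over six months, and "Among the 2620 INR > 2, 330 (12%) were higher than 4.5". The same paragraph says the frequency was stable over time but "differed considerably between departments (10% to 23"%).
- **Main model.** Under Statistical analyses: "the effect linked to the period will be considered fixed and that linked to the prescription tool will be considered random". Department appears in that section only in a comparison of baseline characteristics. The Abstract adds patient and physician clustering, but not department.

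**The concern.** The tools are compared across calendar time, so anything that changes the average overdose risk between blocks competes with the tool as an explanation. Department mix is such a factor by the protocol's own account: the rate differs about twofold between departments, and the number of departments on the system is growing. A high-rate department that starts using order entry partway through a semester contributes INRs to the tools running after that date and none to those running before it. The model as stated cannot separate this from a tool effect.

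Both main aims are exposed: either tool against no support, and personalised against non-personalised. The second is the more sensitive if the true difference between the two tools is smaller than the effect of either one.

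**Working it through.** **The plan's own figure.** Base rate: 330/2620 = 12.6%, given as 12%. Sample size for two proportions, two-sided 5%, 80% power, one untreated to k = 2 treated, with p1 = 0.12 and p2 = 0.12 × (1 − RRR), where p̄ = (p1 + 2·p2)/3 and q = 1 − p:

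n(control) = [1.96·√(1.5·p̄q̄) + 0.84·√(p1q1 + p2q2/2)]² / (p1 − p2)², total = 3n.

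This gives 2442 / 1287 / 768 / 495 for RRR 30/40/50/60%, against the stated 2500 / 1300 / 800 / 500. The stated figures reproduce; the concern is not with them.

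**Inputs for the bias check**
- From the protocol: nine two-month blocks, three per semester, in a 3×3 Latin square. The actual order is in the missing figure, so all 12 possible squares were tried.
- From the protocol: existing departments at 12%; a joiner at 10% or 23%, the two ends of the stated range.
- Assumed, not in the documents: the joiner adds w = 20% or 50% to existing INR volume; existing volume is equal across blocks; there is no true tool effect.
- The outcome is the plan's own planning proxy, INR above 4.5 among INR above 2. The endpoint itself is a proportion of observation time.

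**What cancels.** In semester s a tool occupies block 3(s − 1) + position. In a Latin square each tool takes each position once, so its block numbers sum to 3(0 + 1 + 2) + (1 + 2 + 3) = 15, the same for every tool. Linear growth of a joining department therefore gives tools-versus-control and C-versus-B ratios of 1.000 in every square. Entry at block 4 or block 7 affects two or one blocks of every tool alike, so the ratio is again 1.000.

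**What does not cancel.** If entry falls at the second or third block of a semester, some tools have one more affected block than others. With k affected blocks out of three and joiner rate q, a tool's expected rate is

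r(k) = (3 × 0.12 + k·w·q) / (3 + k·w).

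The contrast is most extreme for entry in the last semester, when k is 0 for some tools and 1 for others:

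| Joiner | r(0) | r(1) | Extreme ratios |
|---|---|---|---|
| 10%, adds 20% | 12.00% | 0.380/3.2 = 11.875% | 0.990, 1.011 |
| 10%, adds 50% | 12.00% | 0.410/3.5 = 11.71% | 0.976, 1.024 |
| 23%, adds 20% | 12.00% | 0.406/3.2 = 12.69% | 0.946, 1.057 |
| 23%, adds 50% | 12.00% | 0.475/3.5 = 13.57% | 0.884, 1.131 |

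Over all 12 squares and all six mid-semester entry points, these are the limits for both tools-versus-control and C-versus-B. Earlier entry gives smaller distortions: for a 23% joiner adding 20%, first-semester entry gives tools-versus-control ratios of 0.961 to 1.041.

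**Period terms.** The joiner at 23% adding 20% raises a block's rate to (0.12 + 0.2 × 0.23)/1.2 = 13.83%, up 1.83 points. One extra affected block in three shifts a tool's mean by 1.83/3 = 0.61 points. Semester and position are balanced against tool in a Latin square, so adjusting for both leaves this in place: the residual is up to about 0.6 points (adding 20%) or 1.3 points (adding 50%, with blocks weighted by volume).

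**Department term.** Within each department the rate is constant in this scenario, so stratifying by department gives a ratio of exactly 1.00.

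**Scale.** Treating INRs as independent, 80% power is reached for an RRR of 12.8% with 15,000 INRs (3 × 5000), or 17.4% with 7860 (3 × 2620, those above 2). The largest spurious reduction above is 11.6% (1 − 0.884).

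**The case against.** **The Latin square already protects the comparison.** In part it does. The Background describes a gradual spread since January 2003, and gradual, linear growth cancels exactly. A reader might infer that any growth in the number of departments will be read as a tool effect; the documents do not support that. Only entry or a mix change inside a semester leaks, and no passage says when departments would join.

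**The joiner sizes are pessimistic.** A department at 23% sits at the top of the observed range, and adding 20% of volume exceeds the average share of the present six (about 17%). The Background also says that several heavy users of antithrombotic drugs are already on the system. This stands: with a joiner at 10% adding 20%, the bias is about 1%.

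**Clustering may absorb it.** The Abstract promises patient and physician clustering, and the sample size section foresees a possible analysis by prescriber. Doctors and patients sit largely within departments, so part of the difference could be absorbed. The Statistical analyses section, however, does not carry these terms into the stated model.

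**An article need not list every covariate.** That is fair for detail left unsaid. Here the model is stated, the population is left open, and the protocol itself reports that the omitted factor varies about twofold.

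**Carry-over.** A reader might also infer carry-over from one tool to the next. The documents give no figure for persistence, and the Background reports that the authors' earlier alternating-period study changed practice without affecting learning. No size can be attached, and it is not part of this point.

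**Conclusion.** The point holds in a limited form. The stated main model leaves the tool contrasts open to bias from a change in department mix inside a semester. It is not a demonstrated bias, and no stated number is wrong. Under the assumed joiner sizes the distortion runs from negligible (about 1%, low-rate joiner adding 20%) through about 5% to 6% (23% joiner adding 20%) to about 12% to 13% (23% joiner adding 50%). Only the last is close to what the full study could detect, and then only on the naive assumption of independent INRs and counting all tests. The direction depends on the order of tools and the entry date, so it could create or hide an effect.

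That one tool runs hospital-wide in each block is inferred from the text, because the schedule figure is not shown. The absence of a closed department list is likewise what the text leaves open, not a statement that departments will join. The change is worth making because it is nearly free.

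**What to change.** In Statistical analyses, add department to the main model as a fixed effect or stratum, alongside period and tool. The section on assessing overdose says that the hospitalisation unit is extracted with every INR result, so no new data are needed. This also covers shifts in mix among the departments already on the system, which a closed list alone would not.

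As a sensitivity analysis, repeat the main comparison in departments using drug order entry at study start. Keep all eligible departments in the main analysis, so that the inclusion of all patients stands.

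The cost is a few extra model parameters and one extra analysis. Neither the schedule nor the software has to change. A department term does not deal with changes in patient mix within a department over time.

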#### Physicians

All doctors authorised to prescribe drugs in the participating departments will be included in the study: residents and fellows, registered and non registered university hospital doctors. Each six-month period will coincide with an internship semester.

### Intervention

To prescribe a drug using Dx-Care^®^, the doctor selects the required drug from an exhaustive list. This opens up a dialogue box in which the doctor types the dose, the frequency of intake and the mode of administration. From this window, it is possible to add a text comment or to consult particular protocols that have been defined by the departments.

It is planned to integrate two types of decision support systems into the computerised prescription program:

1) non-personalised active system: when the drug is selected a window automatically opens giving the prescribing the nomogram for the adjustment of OAT doses in the form of a table (see Tables 2 and 3).

2) personalised active system: when the drug is selected a window automatically opens suggesting a dose recommended according to the nomogram (taking into account the doses previously received by the patient and the patient's INR), together with a date for next INR control and an explication.

